**Methods:**

This will be a quasi-experimental study utilizing qualitative and quantitative methods. During the formative phase, data will be collected through focus group discussions, in-depth interviews, and key informant interviews to explore the barriers and facilitators of provision and utilization of ASRH services. A quantitative design will be used to obtain baseline and endline data through household surveys and client exit interviews. Following the formative and baseline household and client exit assessments, an intervention focusing on provision of ASRH service package targeting boys and girls will be implemented for 18 months. The package will include contextualized ASRH services, including counselling and age-appropriate, comprehensive sexual education for behavior change with an aim to increase utilization of ASRH services. An analysis of the primary outcome (utilization of ASRH services) will be undertaken to establish the difference in difference between the control and intervention arm, before the intervention (using the baseline survey data) and after the intervention (using the endline survey data).

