## Background

The World Health Organization defines “adolescents” as individuals in 10–19 years old and “youth” as 15–24 years old [1]. Together, adolescents and youth are referred to as young people, encompassing the ages of 10–24 years. There is a gap in adolescents’ access to sexual and reproductive health (SRH) services and information, which has not been fully addressed. Several studies have assessed what works to increase access and utilization for SRH among young people. There is, however, a lack of scientifically sound data on the effectiveness of services that target young people in sub-Saharan Africa, especially in comparison to the magnitude of adolescent SRH (ASRH) challenges in the region [2]. Systematic reviews of available published literature suggest that current interventions targeting youth tend to have significant positive effects on improving their knowledge, and sometimes attitudes, regarding sexual behavior, but are less effective in demonstrating change in sexual behavior outcomes [3]. A review of best practices used in ASRH programs established that many ASRH interventions are implemented in an uncoordinated and piecemeal fashion, hence, they do not result in positive outcomes for adolescents [3].

Kenya has poor ASRH indicators. Adolescent pregnancy is a major problem in Kenya, with a teenage pregnancy rate of 18%, and an unmet need of family planning (FP)—as measured by the contraceptive prevalence rate among sexually active, unmarried girls aged 15–19 years—of 49% [4]. It is estimated that about 13,000 girls drop out of school annually in Kenya due to early and unintended pregnancy [5]. Adolescent pregnancy also increases the risk of maternal and newborn deaths and disability, including from complications from unsafe abortion, prolonged labor, childbirth, and the postnatal period [6].

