### Study population

Participants for the qualitative phase of the study will be drawn among adolescents, community members, teachers, healthcare workers, and county health managers in the two counties in the intervention area only, as the findings will be used to shape the intervention. Study participants for the quantitative phase of the study will be adolescents aged 15–19 years. The client exit interviews will target boys and girls aged 15–19 years, who have received any ASRH service at a facility or outreach point. The household survey will target girls aged 15–19 years old who haven’t had their first birth. This is because the unit of measure will be utilization of ASRH services, specifically the use of FP services for primary prevention of pregnancy.

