#### Quasi-experimental design

We will conduct a cross-sectional household survey to collect quantitative data to measure knowledge, attitudes, practices, and uptake of ASRH services. The indicator used to compute the sample size was the FP services utilization rate among adolescents aged 15–19 years, using the most current data from the study areas obtained from the Kenya health information system. The FP utilization for both groups was computed and the lowest prevalence of the two was used in computing the sample size to guarantee the maximum possible sample size. An intra-class correlation of 0.03 was assumed resulting in a design effect of 1.87. The study is powered to detect a 15-percentage point difference between the two groups in each county, 95% confidence interval, with power of 80%. Furthermore, we account for a 10% loss due to possible non-responses and incomplete data. Using the parameters described, the sample size was determined to be 264 per arm (total 528) and 231 per arm (total 462) per arm in Kisumu and Kakamega counties, respectively, at each data collection period. A sample size of 990 participants will therefore be interviewed at baseline, and a similar number at endline. Community units are made up of villages, which, for the purpose of sampling, will be “cluster units.” Since the total number of units in each cluster unit and ward is known, villages will be randomly selected; eight villages in Kobura ward and eight from Kajulu ward in Kisumu County. In Kakamega, seven villages in Kholera ward and seven villages in Bunyala West ward. The sample size will be equally distributed among the selected villages in each ward. Households will be selected through systematic random sampling at an interval of 100–200 m from a particular landmark, until the required sample size is achieved for each ward. In households with multiple adolescents, the Kish method will be used to randomly select one individual from each household [10].

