### Study eligibility criteria

Adolescent boys and girls aged 15–19 years:

• Living, at the time of the survey, in the study sites

• Voluntarily provides informed consent (emancipated minors/adolescents aged 18 and 19 years)

• Voluntarily provides assent coupled with parental permission for minors

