### Study outcomes

Our primary outcome will be FP utilization among adolescents as defined as follows:

• *Number of sexually active girls reporting use of modern contraceptive methods*

• *Number of sexually active adolescents aged 15–19 years sampled*

Sexually active girls will be defined as those who report ever having sexual intercourse. Other secondary outcomes will be knowledge and attitude on the use of modern contraception, among others as outlined in Table 3.

**Table 3 Tab3:** Study outcomes

Other study outcomes among 15–19 years		
Knowledge	Attitude	Practice/utilization
Risks faced by adolescents in pregnancy/childbirth	Toward contraceptives	Utilization of FP services
Available methods of FP	Toward ASRH services offered in facilities/communities/schools	Sexual experience – delay in age at first sex
Secondary study outcomes among 15–19 years: Reduced teenage pregnancy rates in intervention group		

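### The stated 80% power counts every surveyed girl, but the primary outcome counts only sexually active girls; the plan must restate power for that group and say to whom the 15 points apply.

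*Protocol article*

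**What the plan says.** The Study outcomes section defines the primary outcome as a proportion. Its numerator is "Number of sexually active girls reporting use of modern contraceptive methods" and its denominator is "Number of sexually active adolescents aged 15–19 years sampled". Sexual activity is a lifetime self-report: "Sexually active girls will be defined as those who report ever having sexual intercourse".

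The survey population is wider. Under Study population, "The household survey will target girls aged 15–19 years old who haven’t had their first birth". The eligibility list covers age, residence ("Living, at the time of the survey, in the study sites") and consent or assent, with no condition on sexual activity. One adolescent per household is drawn by the Kish method.

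The sample size, under Quasi-experimental design in the Sampling section, starts from another indicator: "The indicator used to compute the sample size was the FP services utilization rate among adolescents aged 15–19 years", taken from the Kenya health information system. The value is not printed. The other inputs are an intra-class correlation of 0.03, a design effect of 1.87, a 15-point difference in each county, 80% power, a 95% confidence level and a 10% allowance for non-response and incomplete data. The result is 264 per arm in Kisumu (eight villages per arm) and 231 per arm in Kakamega (seven villages per arm) at each survey round.

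**The concern.** Girls who have never had intercourse are outside both parts of the primary outcome ratio. They are interviewed and counted in the sample size but contribute nothing to the primary comparison, and nothing in the calculation allows for them. The protocol expects such girls: it lists delay in age at first sex among its outcomes and describes the target group as mainly in school.

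The sizing indicator also differs from the outcome. One is a health-system FP utilization rate among adolescents; the other is self-reported modern method use among girls who have ever had sex. A rate for the first group need not be the rate for the second.

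At stake is the meaning of the 80%. As written, it does not describe the outcome to be tested. A county-level result without a clear effect could be read as evidence of no effect when the precision was lower than the reader was told.

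**Working it through.** **Inputs from the protocol:** intra-class correlation 0.03; design effect 1.87; 15-point difference; 80% power; 264 and 231 per arm; 8 and 7 villages per arm; 10% loss. **Assumed:** two-sided 5% test; sexually active share s from 30% to 90% (not given); the same share in every village.

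**Step 1. Structure of the stated sizes.** The design effect 1 + (30 − 1) × 0.03 = 1.87 implies 30 analysed girls per village. Kisumu: 8 × 30 = 240, and 240 × 1.10 = 264. Kakamega: 7 × 30 = 210, and 210 × 1.10 = 231. Both stated sizes are recovered with every girl analysed.

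**Step 2. Implied baseline rate.** Effective sizes per arm are 240/1.87 = 128.3 and 210/1.87 = 112.3. The two-proportion formula with pooled variance under the null is

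n = [1.96 √(2 p̄(1 − p̄)) + 0.842 √(p₁(1 − p₁) + p₂(1 − p₂))]² / 0.15², with p₂ = p₁ + 0.15 and p̄ their mean.

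For Kisumu, p₁ = 0.171 and p₂ = 0.321 give (1.194 + 0.505)²/0.0225 ≈ 128. For Kakamega, p₁ = 0.129 gives about 112. The unpooled formula gives 0.179 and 0.136. The implied baselines are thus about 17–18% and 13–14%. At these rates 240 and 210 girls give 80%, with no slack.

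**Step 3. Power when only a share s is analysable.** Hold 15 points among active girls and keep the implied baseline. Active girls per arm are 240s or 210s, the design effect is 1 + (30s − 1) × 0.03, and the effective size is their ratio. Power is Φ{[0.15 √n − 1.96 √(2 p̄(1 − p̄))] / √(p₁(1 − p₁) + p₂(1 − p₂))}. For Kisumu at s = 50%: 120/1.42 = 84.5, so Φ[(1.379 − 1.194)/0.600] = Φ(0.31) = 62%.

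| Active share | Active girls per arm (Kisumu / Kakamega) | Design effect | Effective size | Power, each county |
|---|---|---|---|---|
| 100% | 240 / 210 | 1.87 | 128.3 / 112.3 | 80% |
| 90% | 216 / 189 | 1.78 | 121.3 / 106.2 | 78% |
| 70% | 168 / 147 | 1.60 | 105.0 / 91.9 | 72% |
| 50% | 120 / 105 | 1.42 | 84.5 / 73.9 | 62% |
| 30% | 72 / 63 | 1.24 | 58.1 / 50.8 | 47% |

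**Step 4. Sensitivity to the baseline rate.** If the same users are divided by active girls only, the rate becomes p₁/s. At s = 50% that is about 34% in Kisumu and 26% in Kakamega, with power of 51% and 49%. With a baseline near 50% (computed at 49%), Kisumu has about 50% power at s = 50%, and 68% even if every girl is active.

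**Step 5. The other reading of the 15 points.** If the 15 points apply over all girls and all users are sexually active, the difference among active girls is 15/s points. In Kisumu at s = 50%, the rate goes from about 34% to 64% and power is about 98%; at s = 70%, about 91%. At s = 30% the reading fails in Kisumu, since 17.1/0.3 + 15/0.3 = 107%.

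**Step 6. Pooled counties.** Net girls per arm are 240 + 210 = 450. At s = 50% the effective size is 225/1.42 = 158.5. A simple endline contrast of 15 points has about 88% power at a 17% baseline and 85% at 20%. At s = 30% (135/1.24 = 108.9) it has about 70% at a 20% baseline.

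**The case against.** The strongest reply is that the 15 points belong to the same all-adolescent indicator as the baseline. Step 5 then applies, and power among active girls can exceed 80%. This stands as a possible reading. The protocol does not say which population the 15 points describe, so a reader might infer that 80% is certainly not delivered, and the documents do not support that. They support only that the figure was not computed on the stated outcome.

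Pooling also stands in part. The Data analysis section contrasts intervention and comparison sub-counties and names no county-specific test, and Step 6 shows adequate pooled power at some shares. But the power claim is made for each county.

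A reader might take 49% as the true baseline, because the Background gives a national figure "as measured by the contraceptive prevalence rate among sexually active, unmarried girls aged 15–19 years—of 49"%. That sentence introduces the number as unmet need and then describes it as prevalence of use, so it is unclear which it is. It also concerns unmarried girls nationally, whereas the study wards were chosen for low FP utilization. It shows only how power behaves near 50%.

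A much lower rate among active girls could offset the loss: a 5% baseline at s = 50% gives 84.5% in Kisumu and 79.4% in Kakamega. This is unlikely, since removing never-active girls from the denominator would normally raise the rate.

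Surveying all girls is not itself a fault; the knowledge, attitude and age-at-first-sex outcomes need them. The abstract's label, "An analysis of the primary outcome (utilization of ASRH services) will be undertaken", is broader than the operational definition, but Study population and the Phase 2 section narrow it to FP use. A reader might infer a competing primary outcome; it is an editorial point. The power of the difference-in-differences contrast is a separate matter and is not counted here.

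**Conclusion.** The concern holds in limited form. The per-county 80% needs every net girl in the analysis and uses a different indicator, while the primary outcome excludes girls who have never had intercourse. With 15 points among active girls, the implied baselines and a design effect that falls with cluster size, power drops from 80% to about 78%, 72%, 62% and 47% at active shares of 90%, 70%, 50% and 30%. A baseline nearer 50% lowers it further. The active share and baseline are not in the document, so the size is a range. Under the all-girls reading of the 15 points there may be no shortfall. Under either reading the plan has to state what it means.

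**What to change.** In the Quasi-experimental design section, keep the sample size and:

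- state the expected sexually active share among surveyed girls;
- give a baseline rate for the outcome as defined under Study outcomes, taken from the baseline survey rather than from the ambiguous 49%;
- state whether the 15 points apply to all surveyed girls or to sexually active girls;
- restate the power or detectable difference among sexually active girls, for each county and pooled.

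Use the Study outcomes definition as the primary outcome label throughout, including the abstract.

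The cost is rewording and probably a less favourable stated power. No extra participants are needed.

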#### Phase 2: quasi-experimental design

A quasi-experimental evaluation design is proposed to evaluate the rollout of the ASRH program intervention to determine the effectiveness of a combined model to improve utilization of ASRH services. In both counties, program intervention and comparison groups will be selected, while taking measures to ensure that the comparison group matches the program intervention group in general composition, such as possession of similar sociodemographic characteristics. Using the stratified cluster sampling approach, a pre-intervention and post-intervention household survey will be conducted in the two study arms targeting adolescent girls at baseline and endline. The aim of the survey will be to establish the status of adolescents’ knowledge, attitude, and utilization of ASRH services, primarily FP. Implementation of the program intervention will be population-based, targeting adolescent boys and girls aged 15–19 years in the intervention areas. An analysis of the primary outcome (utilization of FP services) will be undertaken to establish the difference in difference between the control and intervention arm, before the intervention (using the baseline survey data) and after the intervention (using the endline survey data).

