In the comparison group, implementation of ASRH services will continue in the same manner as they are routinely or currently being implemented through health facilities. Health workers will be trained to provide adolescent-friendly services. An endline assessment will be done at the end of the 18 months’ implementation period. The table below presents a summary of the package of interventions that will be done in the two study arms.

The Table 2 presents a summary of the package of interventions that will be carried out in the two study arms.

**Table 2 Tab2:** Summary of package of activities by evaluation group

	Program intervention group	Comparison group
ASRH service delivery at facility level	✓	✓
ASRH service delivery at community level	✓	✗
ASRH service delivery in schools	✓	✗
Targeted social behavior change communication	✓	✗

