### Data analysis

Data from in-depth interviews, FGDs, and key informant interviews will be transcribed, translated, and back translated then entered in qualitative data software (Atlas ti.8). We will then develop a coding frame using a grounded theoretical framework. Independent analysis will be conducted by different analysts and subsequent comparison between the developed coding matrices will be used to develop a reliability factor for the analysis. The trends from the emerging themes will be iteratively developed by repeatedly analyzing data collected at different time points. Verbatim generated alongside the code matrix will be used to support the emerging thematic framework.

Descriptive analysis of quantitative variables will be done using measures of central tendency (mean, median) and measures of dispersion (range, standard deviation), as appropriate. The inter cluster correlation will be computed. We will then conduct an exploratory analysis to compare outcomes by the sociodemographic, cultural, and economic characteristics (age, education, religion, marital status, life skills, wealth quintile, place of residence [urban or rural]) using the Rao-Scott chi-square test to see if there is any association. To determine the relative importance of these factors on the outcomes, generalized estimating equations, univariate, and multivariate logistic regressions will be used to adjust for clustering within the clusters. Results from the regression analysis will be reported as odds ratio and 95% confidence intervals.

For the quasi-experimental design, our hypothesis is that adolescent girls in the intervention study arm will have greater increases in FP utilization and improved knowledge and attitudes than girls in the control arm. We will estimate the intervention effect by subtracting the baseline FP utilization rate from the estimates at endline then calculating the difference between the comparison and intervention sub-counties (the difference-in-difference analysis). The difference-in-differences analysis assumes a common trend in the outcome in both the intervention and comparison area. We will measure potential confounders at baseline and endline and adjust our analysis for any compositional changes over time in these confounders. All statistical analysis will be considered statistically significant for *p*-values less than 0.05.

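### Delay in age at first sex is a poorly fixed outcome for two cross-sections of girls aged 15–19: a mean or median age among girls who have had sex would usually stay flat or fall slightly if first sex were truly delayed

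*Protocol article*

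**What the plan says.** The Practice/utilization column of Table 3 (Study outcomes) lists, under sexual experience, "delay in age at first sex". No estimator or analysis population is given for it.

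The data that fit this outcome come from the household survey:
- Sampling, Quasi-experimental design: "We will conduct a cross-sectional household survey".
- Phase 2: "a pre-intervention and post-intervention household survey will be conducted in the two study arms targeting adolescent girls at baseline and endline". Nothing indicates that the same girls are followed.
- Study population: "The household survey will target girls aged 15–19 years old who haven’t had their first birth".
- Description of intervention: "An endline assessment will be done at the end of the 18 months" of implementation.

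On analysis, the Data analysis section says: "Descriptive analysis of quantitative variables will be done using measures of central tendency (mean, median") and measures of dispersion, as appropriate. For associations it names the Rao-Scott chi-square test, logistic regression and generalized estimating equations. It spells out the difference-in-difference calculation only for the family planning utilization rate. No method for censored ages appears. The Study outcomes section defines sexually active as ever having had intercourse.

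**The concern.** An age at first sex exists only for a girl who has already had sex, and it cannot exceed her current age. Two things follow in a survey of 15–19 year-olds taken 18 months after the programme starts. Many of the reported ages refer to events before the programme and cannot respond to it. A girl whose first sex the programme postponed past the interview has no age to report, so she leaves the summary.

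At a given current age, the reports lost this way come from the late end of the distribution. A mean or median among the remaining girls therefore tends to fall when the programme works. At stake is one outcome, not the primary. A reader of the results could take a flat or slightly lower mean age as evidence that the programme did nothing, or that it brought first sex forward.

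**Working it through.** The protocol prints no figure for this outcome, so there is none to reproduce.

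**Inputs from the protocol.** Girls aged 15–19; at most 1.5 years of exposure before endline; 264 + 231 = 495 girls per arm per round; intra-class correlation 0.03 and design effect 1.87. The last two agree with 30 girls per village: 1 + (30 - 1) × 0.03 = 1.87.

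**Assumed, because not given.** Current age is uniform from 15 to 20. Age at first sex is Weibull from age 10, with shape 2, 3, 4 or 6 and median 16, 17, 18 or 19 (16 combinations). The programme multiplies the rate of first sex by 0.7 in the last 1.5 years before interview. There were 1,000,000 simulated girls per combination.

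**Results for a 30% cut, selected combinations, all girls:**

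| Shape, median | Share of reported ages before the programme (no effect) | Change in mean age among girls who have had sex (years) | Ever had sex | First sex in window, among girls not active at its start |
|---|---|---|---|---|
| 2, 18 | 0.719 | -0.151 | 0.454 to 0.418 | 0.189 to 0.137 |
| 3, 18 | 0.620 | -0.139 | 0.439 to 0.395 | 0.229 to 0.168 |
| 4, 18 | 0.547 | -0.109 | 0.431 to 0.380 | 0.256 to 0.189 |
| 6, 18 | 0.444 | -0.053 | 0.423 to 0.368 | 0.290 to 0.221 |
| 6, 16 | 0.656 | +0.007 | 0.785 to 0.738 | 0.557 to 0.461 |

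Across the 16 combinations:
- The share of reported ages that predate the programme ran from 39% to 76%, and exceeded half in 14.
- The mean fell in 15 of 16.
- The exceptions at this and other effect sizes all had the steepest onset (shape 6). One reason is that younger girls lose proportionally more reports, which shifts the pooled mix towards older girls and pushes the mean up.

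A separate simulation with a rising or a flat rate of first sex from age 12 agrees. The mean moved from 15.49 to 15.36 and from 14.59 to 14.45, while ever-sex fell from 0.429 to 0.388 and from 0.418 to 0.391.

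**Restricted to girls without a birth.** With the programme also allowed to avert births, the mean fell in 14 of 16 combinations (about 0 to -0.19 years). The other two were flat or +0.02. Ever-sex and in-window first sex moved the right way in all 16.

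**Sampling error, shape 3 and median 18.** The four cells are the two arms at the two rounds. The standard deviation of reported age is 1.84.
- Mean age: taking 42% ever active, 495 × 0.42 = 207.9 per cell. SE = 1.84 × √(4 × 1.87 / 207.9) = 0.349; z = -0.139 / 0.349 = -0.40. Recomputing the design effect for the smaller cluster take (30 × 0.42 = 12.6, giving 1 + 11.6 × 0.03 = 1.348) lowers the SE only to about 0.30.
- Ever-sex: SE = √[1.87 × (3 × 0.439 × 0.561 + 0.395 × 0.605) / 495] = 0.061; z = -0.044 / 0.061 = -0.72; power about 11%.
- In-window: girls not active at the start are 1 - 0.439 × 0.620 = 0.73 of the sample, so 361 per cell. SE = √[1.87 × (3 × 0.229 × 0.771 + 0.168 × 0.832) / 361] = 0.059; z = -0.061 / 0.059 = -1.04; power about 18%.

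With a 50% cut, power is about 24% for ever-sex and 45% for the in-window measure.

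**The case against.** The strongest reply is that the protocol never commits to averaging ages among girls who have had sex. The sentence on mean and median is generic and qualified by appropriateness. The table entry begins with sexual experience, which can be read as ever having had sex. The inferential methods named suit binary outcomes, and a median can be estimated with never-active girls kept as censored. The estimator for a secondary outcome is commonly left to an analysis plan, which is not shown here. All of this is correct. A reader might infer that the trial, run as written, would report the wrong sign; the document does not support that, because the estimator is open and the expected shift is well inside sampling error.

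A reader might also infer that a delay cannot be shown at all from these surveys. That is too strong: the same reports, analysed with never-active girls kept in, move the right way. Nor can it be said that most reported ages predate the programme. That depends on an onset distribution the protocol does not give, and it failed in 2 of 16 combinations.

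Another objection is that restricting the survey to girls without a birth undermines the replacement, since averting births keeps more active girls eligible and pushes ever-sex up. The restricted simulation did not bear this out under its assumptions, but the restriction remains a limitation.

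What survives is more than silence. The outcome is named as an age to be delayed, in a design where age is observed only for those already active, and none of the methods named keeps the others in as an age.

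**Conclusion.** The outcome is badly fixed for this design and should be redefined. If ages are summarised among girls who have had sex, a real 30% cut in the rate of first sex would, under most assumed onset distributions, leave the mean unchanged or lower it by up to about 0.2 years. With a standard error of about 0.35 years the observed result would mostly be noise, so the summary would be uninformative and tilted against the effect sought. The size rests entirely on assumed onset distributions. The direction is consistent across most of them, and the exceptions occur only with very steep onset. The point concerns an outcome other than the primary and leaves the family planning analysis untouched.

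**What to change.** Replace the Table 3 entry with one of two definitions, compared by difference-in-difference with adjustment for clustering:

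- The age-adjusted proportion of all surveyed girls who have ever had sex. This follows the definition already in Study outcomes and suits the logistic and GEE methods already named.
- If age or date of first sex is recorded at both rounds, first sex within the 18 months before each survey, among girls not yet active at the start of that window. Girls still not active stay in as censored. The baseline round uses the same look-back.

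State that mean or median age among girls who have had sex will not be compared between arms.

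The first option needs only a change of definition. The second needs the timing of first sex in both questionnaires and brings recall error in dates; if baseline timing is not collected, only the first option remains. Power is low either way (about 11% and 18% for a 30% cut in the worked case). Report the result as an estimate with its confidence interval, do not read a non-significant result as no effect, and note the restriction to girls without a first birth.
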